### **3.3. The need for personalized risk-based screening**

Current BC screening guidelines are primarily based on age and do not support regular screening of women below the age of 50. This largely excludes young women at high risk for developing BC. On the other side, mammography screening has also potential harms and costs, therefore it is not reasonable to implement screening for all women under the age of 50. It is no longer appropriate to apply a single recommendation to women across all age groups and risk profiles and a far more precise and personalized risk estimation is needed. Screening with mammography reduces BC mortality risk 20-40% (3-5). The decline varies across age groups, ranging from 8% in the age group 39-49 years to 33% in the age group 60-69 years. The largest decrease in mortality has been shown in the age group 50-69 years, the evidence base for efficacy is weaker in younger women. The relationship between benefits and potential harms for screening in the age group 40-50 years has been controversial and in most countries

screening is not offered in this risk group. Reduced BC deaths may come at the expense of overdiagnosis (the identification and unnecessary treatment of clinically insignificant tumors), as well as the consequences of false-positive or false-negative results (5, 8).

An age-based population-level breast screening strategy that reduces BC mortality but does not account for the wide variation in individual women's cancer risks. A woman's risk of developing BC is influenced by many factors, but BC screening recommendations are based primarily on age. There are disagreements in the medical community about the optimal age to begin BC screening, as well as the frequency of screening and the age at which to stop. In Norway and mostly globally, the current BC screening guidelines do not support regular screening of women at younger ages than 50 years, thereby largely excluding potentially high-risk women from screening in younger age groups. The relationship between the benefits and potential harms of screening in the age group under 50 years has been controversial and screening is not recommended for all women under age 50. The application of personalized risks is necessary to identify those women who could benefit from the earlier start of the screening. Also, for high-risk women over age 50 current screening with 2 intervals is not optimal and may miss interval cases.

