### 3.7. Background Summary and Study Rationale

The current 'one-size-fits-all' BC screening approach does not consider individual risks of women and there is a need for more precise screening which considers individual risks of women.

BC screening is widely implemented in many healthcare systems to reduce BC mortality through earlier diagnosis. Also, in Norway screening is offered to women in age 50-69 with mammography after every 2 years. Screening with mammography reduces BC mortality risk 20-40% among women at age 50-69. But approximately 20% of BCs occur in women younger than 50 years. The relationship between benefits and potential harms for screening in the age group under 50 years has been controversial and, in most countries, as well as in Norway, screening is not offered in this risk group.

For a personalized approach, we need tools for risk stratification. Around 30% of the total BC risk has been shown as hereditary, therefore genetic predisposition tests serve as tools for risk estimations. These tools are already in clinical use in the form of polygenic risk score (PRS) tests and monogenic pathogenic variants' (MPV) tests, and these can serve as BC risk prediction instruments for personalized prevention. Also, BD in mammography is a tool for BC risk prediction and more precise recommendations for screening. We have developed a new model for a genetic risk-based BC screening program that enables personalized prevention based on individual risk levels.

The screening plan should depend on a woman's risk for BC and personal preferences. The use of genetic risk scores and mammographic BD identifies women that are at increased risk of developing the disease.

Risk assessment per se does not have inherent clinical utility; the subsequent adoption of a risk-based intervention based on the results of the assessment is what influences the health outcomes. The use of such a strategy depends on whether the risk-based intervention is appropriate, accessible, practicable, and acceptable. To combine individual genetic risk testing, BD information and subsequent healthcare services, it is necessary to create and implement a whole program of personalized genetics-based BC screening and prevention. It is necessary to evaluate: the benefit-harm trade-offs of such strategies and the acceptability and feasibility of implementing risk-stratified prevention and early detection programs.

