#### **In case of PRS only:**

- Age
- Personal medical history

- Family cancer history
- Current medications (hormonal agents)
- Mammography: normal / needs additional specification / tumour
- MD
- Short- and long-term psychosocial aspects related to genetic feedback (questionnaires after the return of data and after 6 months)

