#### Methodology of the cost-effectiveness study

Whereas the whole pilot study aims to develop models for the personalized medicine interventions, it is not possible to predict which efficacy and effectiveness measures will be best suited to estimate the health outcomes of the program.

The planned personalized medicine interventions are preventive, and the pilot project will last less than 2.5 years, thus the most robust health outcome of mortality cannot be achieved during the study. Therefore, additional health outcomes, e.g. disease-free time to diagnosis and/or hospital care, stage of cancer diagnosed will be used to estimate the effect of preventive measures to increase the disease-free life years, postpone the negative health events, and decrease the need to use health care resources will be collected. This data will be used to model the number of events occurring in specified cohorts of persons at risk – a cohort receiving personalized preventive interventions will be compared to that on standard care.

To estimate the long-term effectiveness and costs of the new interventions, economic modeling will be used. The Markov cohort models of the natural history of BC will be constructed to assess the cost-effectiveness of preventive interventions.

The recently published cost-effectiveness studies modelling BC will be used to construct the natural history of the disease. Annual age-specific probabilities of dying from this disease and the health-related quality of life decrement during the illness will be calculated for the Swedish, Estonian and Portuguese cohorts using published cost-effectiveness studies.

The analysis results will be presented as incremental costs and quality-adjusted life-years (QALYs) gained with each intervention compared to no personalized medicine and as incremental cost-effectiveness ratios (ICERs). Both costs and utilities will be discounted at an annual rate of 5%. The sensitivity analysis will be performed by varying one or more similar parameter(s) at a time while holding other parameters at their base case value.

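### The QALY model names quality-of-life loss during illness as its only utility input; built that way, false-positive recall, benign biopsy and risk labelling in healthy women carry no QALY loss

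*Protocol*

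**What the plan says.** Protocol section 6.2, under the methodology of the cost-effectiveness study, describes the model in some detail.

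- Structure: "The Markov cohort models of the natural history of BC will be constructed to assess the cost-effectiveness of preventive interventions".
- Outcomes feeding it: "disease-free time to diagnosis and/or hospital care, stage of cancer diagnosed will be used to estimate the effect of preventive measures".
- Inputs from published studies: age-specific probabilities of dying from the disease, and "the health-related quality of life decrement during the illness will be calculated".
- Result: "incremental costs and quality-adjusted life-years (QALYs) gained with each intervention compared to no personalized medicine", together with ICERs.
- Discounting: "Both costs and utilities will be discounted at an annual rate of 5" per cent.
- Sensitivity analysis: one parameter, or a few similar ones, varied while the others stay at base case.

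Other sections deal with harm. Section 3.3 lists overdiagnosis, "as well as the consequences of false-positive or false-negative results". Section 3.7 says it is necessary to evaluate "the benefit-harm trade-offs of such strategies". Section 5.4 plans questionnaires on "Short- and long-term psychosocial aspects related to genetic feedback", given once results are returned and again at 6 months. No text links these questionnaires to utilities.

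**The concern.** Section 5.2 (Steps 3 and 4) offers some healthy women aged 40-49 mammography that the national programme does not give them, and tells some of them that their risk is raised. More examinations mean more recalls and benign biopsies in women without cancer. None of these events is an illness state, so a decrement that applies only during illness does not reach them. The cost list in section 6.2 includes out-patient care, so recalls and biopsies can enter the model as costs. No matching loss of utility is named.

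The ICER divides incremental cost by incremental QALYs. If the QALY gain per woman is small, even a brief loss shared by many screened women can change the ratio noticeably. For false positives the direction is predictable: the extra examinations belong mainly to the personalised programme, so leaving out their disutility tends to flatter it. The planned sensitivity analysis does not help, because a parameter that is not in the model cannot be varied.

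**Working it through.** The protocol states no utility, QALY or ICER figure, so there is nothing to reproduce. The check is whether the omitted loss could be large relative to the gain.

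**Inputs from the protocol**
- 10-year risk at the screening threshold: 2.1% (section 5.2, Step 3). The same section uses 2 x 2.1% = 4.2% for one-year intervals.
- Reduction in breast cancer mortality: 8% at age 39-49, and 20% as the lower end of the overall range (section 3.3).
- Discount rate: 5% a year (section 6.2).

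**Assumed inputs (not in the protocol)**
- Case fatality 10-20%; 30 life-years lost per death, starting 10 years after entry.
- False-positive rate 3-10% per examination; utility loss 0.05-0.2 for 5 weeks per false positive.
- Examinations over 10 years: five (two-yearly) or ten (yearly).

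**Discount factors at 5%**
- 30 years of life, deferred 10 years: 16.14 / 1.629 = 9.91.
- Five two-yearly examinations: 4.153. Ten yearly examinations: 8.108.

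**Gain per screened woman** = risk x case fatality x mortality reduction x 9.91
- Lowest: 0.021 x 0.10 x 0.08 x 9.91 = 0.0017.
- Highest: 0.042 x 0.20 x 0.20 x 9.91 = 0.0167.

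**False-positive loss per screened woman** = rate x utility loss x (5/52) x discount factor
- Two-yearly: 0.03 x 0.05 x (5/52) x 4.153 = 0.0006, up to 0.10 x 0.2 x (5/52) x 4.153 = 0.0080.
- Yearly: 0.0012 to 0.0156, with 8.108 as the factor.

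| Risk, interval | Mortality reduction | Gain (QALY) | Omitted loss (QALY) |
|---|---|---|---|
| 2.1%, two-yearly | 8% | 0.0017-0.0033 | 0.0006-0.0080 |
| 2.1%, two-yearly | 20% | 0.0042-0.0083 | 0.0006-0.0080 |
| 4.2%, yearly | 8% | 0.0033-0.0067 | 0.0012-0.0156 |
| 4.2%, yearly | 20% | 0.0083-0.0167 | 0.0012-0.0156 |

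In the first row the loss runs from 0.0006 / 0.0033 = 18% of the gain to 0.0080 / 0.0017 = 4.7 times the gain. In the second it runs from 0.0006 / 0.0083 = 7% to 0.0080 / 0.0042 = 1.9 times.

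**Labelling.** A constant utility change over 10 years that equals the gain is gain / 8.108: 0.0017 / 8.108 = 0.0002 at the low end and 0.0167 / 8.108 = 0.0021 at the high end. A very small lasting effect of the label would therefore matter, and it could go either way.

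**Limits of the illustration**
- The gain counts averted deaths only. It leaves out any quality-of-life benefit of earlier-stage diagnosis.
- Counting life-years from screening entry instead of 10 years later multiplies the gain by 1.629.
- A full 10 years of examinations before age 50 fits only a woman who starts at about 40. Section 5.2 starts screening when her risk reaches the threshold, which may be later.

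**The case against.** The strongest reply is that the protocol never says the illness decrement is the only one. It states how two inputs will be calculated and does not close the list. It leaves the effectiveness measures open, and section 4 says that pilot data will feed the model. A full list of disutilities could properly sit in a later analysis or economic plan, which may exist but is not shown. This stands to the extent that the protocol cannot be said to exclude other decrements. It does not remove the point: section 6.2 goes far enough into the utility inputs to name one, and the outcomes it lists for the model are disease events.

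A reader might infer more than the text supports.

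- *All harms are left out.* Overdiagnosed cancers are diagnosed cancers and would carry the illness decrement, provided the model generates them. A pure natural-history model may not.
- *The comparator is free of these harms.* Section 3.4 describes annual mammography from age 40 for women at increased familial risk, and supplementary imaging in clinical mammography. The difference in harm is incremental.
- *Risk labelling can only hurt.* Most of the levels in Step 3 describe raised risk, but the lowest covers women at or below average, who may be reassured. The net sign is unknown.
- *Harm is ignored altogether.* Section 4 defines clinical utility to include harms and psychosocial implications, and section 5.4 collects psychosocial data. Section 3.7 does not say that the trade-off must be expressed in QALYs.

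It is also fair to say that the illustration rests largely on assumed inputs and that its range is wide.

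**Conclusion.** The point holds in conditional form. If the model is built from the inputs that section 6.2 names, false-positive recall, benign biopsy and risk labelling in healthy women have no QALY weight, although the protocol recognises screening harms and asks for benefit and harm to be weighed. Omitting the false-positive loss would tend to favour the personalised programme. The direction for labelling is not known.

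It would go too far to say that the QALY gain is overstated, or by how much. No model result exists, the list of inputs is not declared complete, and the size depends on case fatality, life-years lost, false-positive rate and disutility, none of which the protocol gives. Under the assumptions shown, gain and omitted loss are of the same order, roughly 0.001 to 0.01 QALY per screened woman each. That makes the omission potentially material and worth correcting, but it does not measure a bias.

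**What to change.** In the cost-effectiveness methodology of section 6.2:

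1. Add utility decrements for false-positive recall and benign biopsy from published studies, in the base case or at least in a stated scenario, and include them in the sensitivity analysis.
2. Add a risk-labelling effect that may take either sign, with a range.
3. State that the model generates overdiagnosed cancers, so that they carry the illness decrement.
4. Use the mammography and biopsy results already listed in section 5.4 as a check on event rates. Numbers will be small: even if all 80 women were examined, an assumed 3-10% false-positive rate gives 80 x 0.03 = 2.4 to 80 x 0.10 = 8 events per round.
5. Optionally, add a short generic utility questionnaire before testing and at the two planned psychosocial time points. Section 5.4 lists no pre-test measurement, and a change within each woman cannot be recovered later without one.

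The cost is a few model inputs, slightly more modelling work and, if step 5 is taken up, a short questionnaire. The ICER may become less favourable. Utilities from 80 women will be imprecise, so published values should remain the main source.

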|                                        | Objectives                                                                                                                                                                                                                                                                                            | Outcome Measures                                                                                                                                                                                                                                                                                                                                                                                                                                                                                                                                                                                                                                                         |
| Primary                         | To evaluate the impact of implementing population-based genetics testing strategy for breast cancer precision prevention using the polygenic risk score and monogenic pathogenic variant (MPV) testing in the Norwegian healthcare setting.                                                                  | Elevated-risk breast cancer polygenic risk score and monogenic pathogenic variants prevalence for precision screening - the proportion of women with elevated risk for personalized screening                                                                                                                                                                                                                                                                                                                                                                                                                                                                                   |

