#### Key hypotheses:

- Genetics-based BC prevention program has a clinical utility and is cost-effective for women under age 40 or 50.

- Genetics-based BC prevention program is feasible and acceptable, and healthcare systems are ready to implement that.

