#### **4. OBJECTIVES AND OUTCOME MEASURES**

The general aim is to perform a clinical cohort study that would test issues regarding the deployment of PRS test AnteBC and MPV-based risk testing in the Norwegian clinical setting. This clinical pilot would simultaneously evaluate logistical and ethical considerations (patient risks, feedback, operational procedures), test the flow of information, and would also create prospective performance data for PRS testing. In addition, the project will explore the relationship between PRS and mammographic density (MD).

The target group is healthy women at age 40-49, which is the age group before the current official screening. For genetic risk prediction, the project uses PRS and, if indicated, MPV tests as healthcare services with the following diagnostic screening and prevention activities.

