#### The data used for cost calculations will include

- Direct costs of the use of health care services (out-patient care, hospital care, and pharmaceuticals), based on the data from healthcare systems.
- Costs for developing and maintaining IT solutions for collecting and using health information for personalized medicine purposes.
- Costs for collection and analysis of additional samples arising from the new clinical approaches of the two preventive interventions.
- Costs for disseminating the results of the pilot project to the scale of the whole population: training of health care staff and additional workload estimates related to full implementation of the personalized medicine approach (e.g. motivational interviewing).

Most of this cost data will be collected in parallel to the implementation of the pilot project.

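### The cost-effectiveness method derives breast cancer death probabilities and quality-of-life decrements for Swedish, Estonian and Portuguese cohorts and names no Norwegian cohort, although the study question is Norwegian

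*Protocol*

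**What the plan says.** Under *Methodology of the cost-effectiveness study* in section 6.2, the protocol plans Markov cohort models of the natural history of breast cancer. Two sets of inputs are tied to named countries. One is the yearly probability, by age, that breast cancer is fatal; the other is the utility lost while a woman is ill. Of both, the text says that they "will be calculated for the Swedish, Estonian and Portuguese cohorts using published cost-effectiveness studies". Results are to be given as incremental costs, QALYs and ICERs.

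The study question is set elsewhere. The synopsis states the primary objective as an evaluation of polygenic risk score (PRS) and "monogenic pathogenic variant (MPV) testing in the Norwegian healthcare setting". Section 4 gives the general aim as testing the deployment of the PRS test and "MPV-based risk testing in the Norwegian clinical setting". It adds: "The target group is healthy women at age 40-49, which is the age group before the current official screening". The inclusion criterion in section 5.1 has the same age range, and section 5.2 limits active recruitment to the Vestre Viken hospital area.

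Two other statements bear on the same analysis. The first key hypothesis in section 3.7 says that the programme "is cost-effective for women under age 40 or 50". The cost list in section 6.2 includes sample collection and analysis costs "arising from the new clinical approaches of the two preventive interventions".

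**The concern.** Probabilities of dying from the disease and the utility loss during illness feed directly into the QALYs of a Markov model, and through them into the ICER. If they describe other countries' populations, the result does not describe the Norwegian decision that the study is meant to inform. Cost-effectiveness is a key hypothesis, a research question, part of the secondary aim and a listed secondary outcome, so it is more than a side remark.

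This is not detail left for a later analysis plan. The protocol names specific cohorts, and they are not those of the study. A later plan that followed the protocol would carry the mismatch forward; one that used Norway would contradict it.

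**Working it through.** No formula applies and there is no planned figure to reproduce. The check is a comparison of the protocol's own statements.

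**Country**

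| Item | Where | Country |
|---|---|---|
| Primary objective | Synopsis | Norway |
| General aim | Section 4 | Norway |
| Active recruitment | Section 5.2 | Norway (Vestre Viken) |
| Baseline 10-year risk of 2.1% at age 50, used for the screening recommendations | Sections 3.2 and 5.2 | Norway |
| Probability of dying from breast cancer | Section 6.2 | Sweden, Estonia, Portugal |
| Quality-of-life decrement in illness | Section 6.2 | Sweden, Estonia, Portugal |
| Pilot data, epidemiological data, services and costs as model inputs | Section 4 | Not stated |
| Health care costs | Section 6.2 | Not stated |

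The last two country-specific rows disagree with the four above them. Section 5 describes no Swedish, Estonian or Portuguese cohort, and no reason is given for transferring values from those countries to Norway.

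**Whether the planned sensitivity analysis covers this.** It varies one or more similar parameters while the others stay at their base-case values. It explores uncertainty around a base case and does not replace a base case built for other populations.

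**Whether Norwegian inputs are already in the protocol.** Only in part. Section 3.1 gives Norwegian breast cancer mortality as an age-standardised rate of 22.0 per 100,000 person-years (10.7 on the world standard). These are single population rates, whereas the model needs probabilities by age. NORDCAN is cited only for the 10-year risk of developing breast cancer at age 50. A Norwegian source for age-specific mortality therefore still has to be named, and the protocol gives none for utilities.

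**Age.** The cost-effectiveness text in section 6.2 states no age range for the modelled cohort. The hypothesis in section 3.7 gives two alternative upper limits, 40 and 50, and no lower limit. The enrolled range is 40-49. The under-40 alternative lies wholly outside that range; the under-50 alternative contains it but extends below it. Pilot data can inform the model only for ages 40-49.

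**Interventions.** The cost list refers to two preventive interventions. Section 5.1 describes one programme, while sections 4 and 5.2 describe two testing components, PRS for all women and monogenic testing where indicated. The text does not say whether these components are the two that are meant.

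**Possible origin.** The same method section says that the pilot lasts less than 2.5 years. Sections 5.2 and 5.6 give 10 years of follow-up, and the synopsis a study period from November 2022 to November 2035. Together with the country list, this suggests text carried over from another project. That is an inference; the point does not depend on it.

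**The case against.** The strongest reply is that the consequence is limited. The country list governs two sets of parameters, not the whole model. Section 4 also feeds in data from the clinical pilot, epidemiological data and cost data, and section 6.2 does not tie incidence, risk distribution, uptake or background mortality to the three countries. Cost-effectiveness is one of many secondary outcomes in a pilot of 80 women analysed mainly by description. The primary outcome is unaffected. The model is to be run in the last six months, so its literature-based inputs can be changed without touching enrolment or participant data. Health-economic models also often borrow published values from other countries.

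Most of this stands, and it limits the severity. It does not remove the mismatch: borrowing values can be defended, but the protocol offers no defence and does not name the population to which the values would be transferred.

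Some stronger readings are tempting but not supported:

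- A reader might infer that the model is specified for women under 40. It is not. The model text gives no age, and the phrase in section 3.7 is a loosely worded hypothesis whose second alternative includes women aged 40-49.
- A reader might infer that foreign mortality would be combined with Norwegian costs. The cost list names no country.
- A reader might take the reference to two interventions as an error. It may mean PRS and monogenic testing, so a request for a definition is as far as the text allows.

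**Conclusion.** The country mismatch is real and wrong as written. The method fixes disease mortality and illness utility to three countries, none of which is the study's setting, and leaves Norway out. QALYs and ICERs computed that way would not rest on Norwegian values for either input.

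Its reach is one secondary outcome and two sets of inputs. It would be too strong to say that the model cannot address the Norwegian question at all, because inputs from the pilot would come from the Norwegian study. No numerical shift in the ICER should be attached to the point. That would need the difference in inputs between countries and the model's response to it, and the documents give neither. Assuming that QALY gains move in proportion to breast cancer mortality would have no support in the plan.

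The loose age wording of the hypothesis and the undefined interventions are smaller points, best settled in the same edit. The conclusion rests only on the protocol text; a separate analysis plan was not available and could not be checked.

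**What to change.** 1. In *Methodology of the cost-effectiveness study*, replace the reference to the three countries' cohorts with a Norwegian cohort of women entering the model at age 40-49. Specify Norwegian age-specific breast cancer mortality and name its source.
2. For the quality-of-life decrement, use Norwegian values where they exist. Where they do not, use published values and justify their transfer to Norway.
3. In the cost list, state that health care costs are Norwegian.
4. In section 3.7, align the cost-effectiveness hypothesis with women aged 40-49.
5. In the cost list, define the two preventive interventions, or change the wording if only one programme is meant.

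The cost is small: protocol wording and some work to source Norwegian mortality, utility and cost inputs. Recruitment, data collection and the primary analysis do not change.
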